### Setting

This study is being conducted in two locations: British Columbia Emergency Health Services (BCEHS), which serves the Canadian province’s 5.7 million residents across urban, suburban, and rural settings, and the Columbus Division of Fire, which serves a mostly urban population of 900,000 in the U.S. city of Columbus, Ohio.

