### Automated patient recruitment and randomization

Inclusion criteria for the study are 1) 9-1-1 calls assigned as “suspected” or “confirmed” OHCA, and 2) OHCA confirmed as paramedic-treated, public location OHCA. Exclusion criteria include 1) a traumatic cause of cardiac arrest, 2) cardiac arrest occurring in the context of a dangerous scene as determined by the 9-1-1 call-taker, 3) paramedic-witnessed cardiac arrest, 4) cardiac arrest not treated by paramedics (Do Not Resuscitate or signs of obvious death), 5) cardiac arrest occurring in nursing homes. To operationalize these criteria and facilitate the recruitment of OHCA patients at the time of the 9-1-1 call, we undertake the following processes. All 9-1-1 calls coded as possible OHCA incidents occurring in non-residential locations in the computer-assisted dispatch systems of participating communities are automatically enrolled into the trial and undergo random allocation to a treatment group by the PulsePoint server. In BC, Medical Priority Dispatch System codes 09D01 (ineffective breathing), 09E01 (respiratory arrest), 09E02 (uncertain breathing status), 11D01 (choking with altered level of consciousness), 11D02 (choking with abnormal breathing), 11E01 (verified choking), 12D01 (convulsions with absent breathing), and 14D01 (unconscious drowning) define possible OHCA. In Columbus, Association of Public-Safety Communications Officials (APCO) call designators “Cardiac Arrest”, and “Drowning” are used. When the trial was launched, Columbus had also included “Unconscious Overdose”, and “Unconscious Person”, but these codes were later removed from our randomization trigger criteria due to very low specificity for OHCA. Random allocation occurs using code embedded within the PulsePoint server activation process for “CPR Needed” alerts. The code references a randomization table generated by the study statistician enabling 1:1 random allocation, stratified by site, using permuted blocks of varying sizes. For each eligible 9-1-1 call, the next entry in the randomization table determines group assignment. If allocated to the treatment group, the PulsePoint activation proceeds as designed. If assigned to the control group, the process stops before any “CPR Needed” notifications are sent. Each allocation is automatically logged by the server and used by study staff to track enrollment.

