### Analysis plan

The primary outcome will be compared between treatment groups using the Mantel-Haenszel Chi-square test, stratified by site. Estimates of the treatment effect will be reported as absolute risk differences and relative risks, each accompanied by 95 % confidence intervals. Binary secondary outcomes will be analyzed using the same stratified approach. Continuous outcomes, such as emergency services response time and on-scene time intervals, will be analyzed using the stratified Wilcoxon rank-sum (van Elteren) test to account for non-normal distributions while stratifying by site.

The secondary objective will be addressed using a hierarchical logistic regression model to examine factors associated with the receipt of bystander resuscitation following PulsePoint notification. This model will account for clustering by site and include independent variables such as age, sex, witnessed status, time of day, day of the week, paramedic response interval, number of PulsePoint users in proximity, and whether dispatcher-assisted CPR instructions were provided. Results will be expressed as adjusted odds ratios with 95 % Wald confidence intervals. The same modeling approach will be applied to selected binary secondary outcomes. Subgroup analyses will examine whether the effect of the intervention differs across key subpopulations. These will include a comparison of events in rural versus urban settings, as defined by Statistics Canada census metropolitan area classifications, and a comparison of cardiac arrests with witnessed shockable rhythms versus non-shockable rhythms. Interaction terms will be included in regression models to formally test for effect modification.

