This has been a very challenging trial to implement and manage. Of the five originally proposed study sites, only two were ultimately able to participate. Concerns related to legal liability for the hosting agency, specifically around the randomization of cardiac arrest patients and the sharing of patient data prevented participation of proposed sites in Toronto, Oshawa, and Winnipeg. Despite several years of engagement with these sites and successful technical implementation of the PulsePoint system we were unable to reach a resolution on these issues and efforts to implement the trial in these places were abandoned.

Technical hurdles contributed to significant delays. In British Columbia, accurately distinguishing public from private locations during 9-1-1 calls was essential for determining trial eligibility, as the PulsePoint Respond app was initially designed to notify for public-location arrests only. To support public-only alerts, the Foundation developed custom geolocation coding for BC, and delays in its development, implementation, and testing postponed the site’s launch by several months. The COVID-19 pandemic introduced disruption and delays to trial implementation. Concerns about infection risk among lay responders, paramedics, and firefighters led to a delayed launch of the study for nearly a year. After launch, both active study sites experienced intermittent downtime due to cybersecurity threats, CAD software upgrades, and technical malfunctions. Even after all these issues were resolved, recruitment has been slower than projected, primarily due to limited public uptake of the PulsePoint app and the restrictive inclusion criteria necessary for a scientifically rigorous evaluation. A key contributor to this challenge was the lack of dedicated funding for community outreach, marketing, or communications. The study budget did not include resources for promotional activities, and the hosting agencies, while very supportive, had limited capacity to fund or lead sustained public engagement campaigns. As a result, all efforts to promote PulsePoint uptake in participating communities were conducted in-kind, using low-cost strategies.

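### The secondary-objective model is hierarchical by site, but two sites cannot support a between-site variance; site should enter as a fixed effect

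*Protocol article*

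**What the plan says.** The Analysis plan section of the protocol article addresses the secondary objective with a "hierarchical logistic regression model to examine factors associated with the receipt of bystander resuscitation following PulsePoint notification". On site it says: "This model will account for clustering by site and include independent variables such as age, sex, witnessed status". The other listed covariates are time of day, day of the week, paramedic response interval, number of nearby PulsePoint users and dispatcher-assisted CPR instructions. On reporting it says: "Results will be expressed as adjusted odds ratios with 95 % Wald confidence intervals". The same approach is extended to selected binary secondary outcomes.

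The Setting section says: "This study is being conducted in two locations", namely British Columbia and Columbus. The Discussion confirms the count: "Of the five originally proposed study sites, only two were ultimately able to participate".

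Elsewhere site is a fixed stratum. Randomisation is described as "enabling 1:1 random allocation, stratified by site", and the primary test is the "Mantel-Haenszel Chi-square test, stratified by site". No other level of clustering is named. The article does not say whether the hierarchical model carries site as a random intercept or handles it through robust standard errors.

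**The concern.** A hierarchical model adjusts for site by estimating how much sites vary and shrinking each site's effect accordingly. With two sites there is one contrast from which to estimate that variance. If the estimate falls to zero, the fitted model is an ordinary logistic regression with no site term, although the plan says site is accounted for. If the estimate is small but not zero, the adjustment is partial.

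This matters most for covariates that differ between the sites. British Columbia is a province-wide service covering urban to rural areas and uses MPDS codes. Columbus is mostly urban and uses APCO designators. The number of app users nearby, the response interval and the giving of dispatcher instructions could plausibly differ between them, and these covariates are among those the secondary objective is about. Without full site adjustment, their odds ratios absorb part of the difference between the sites.

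**Working it through.** **The plan's own figures.** The article gives no number for this model, so there is nothing to reproduce directly. Its revised total of 340 serves as an input. The plain two-proportion formula is consistent with it: taking a baseline of 0.35 (an assumption; the article states none) and the planned 15-point difference, n per group = [1.96·√(2·0.425·0.575) + 0.842·√(0.35·0.65 + 0.50·0.50)]² / 0.15² ≈ 170, hence 340.

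**Inputs from the article.** Two sites; a hierarchical logistic model clustered by site; Wald intervals; N = 340, or 170 if the model is fitted only to the treatment group, since it concerns resuscitation after a notification.

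**Assumptions not in the article.** Site split, size of the site difference, and covariate distributions.

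**Step 1: one degree of freedom.** Even if both site effects were observed without error, a 95% interval for the between-site SD would run from √(1/χ²₀.₉₇₅,₁) = 0.446 to √(1/χ²₀.₀₂₅,₁) = 31.9 times the estimate.

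**Step 2: simulation with the site effect drawn at random.** Sites split 70/30; 400 runs per row (200 where the SD is 0). One covariate is balanced over sites; the other has a mean that differs by site. Zero means an estimated SD below 0.01. Coverage of nominal 95% Wald intervals is shown as balanced / differing covariate.

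| True site SD | N | SD estimated at zero | Random intercept | Site-clustered robust | Fixed site |
|---|---|---|---|---|---|
| 0.3 | 170 | 70% | 0.950 / 0.932 | 0.675 / 0.698 | 0.953 / 0.955 |
| 0.3 | 340 | 57% | 0.970 / 0.935 | 0.698 / 0.677 | 0.973 / 0.950 |
| 0.6 | 170 | 50% | 0.955 / 0.930 | 0.667 / 0.627 | 0.960 / 0.955 |
| 0.6 | 340 | 41% | 0.950 / 0.927 | 0.645 / 0.650 | 0.948 / 0.935 |
| 0 | 170 | 90% | 0.950 / 0.945 | 0.680 / 0.665 | 0.950 / 0.940 |

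The Monte Carlo standard error near 0.95 with 400 runs is √(0.95·0.05/400) = 0.011, so the random-intercept shortfall in this table is small and not far outside noise.

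**Step 3: simulation with a set site gap.** This is closer to the actual trial, which has one particular pair of sites. With a 70/30 split, N of 170 to 340 and a site log-odds gap of 0.4 to 0.7, the random-intercept SD was zero in 9–69% of runs. Coverage was 0.94–0.97 for balanced covariates. For covariates differing by site it was 0.90–0.93, with bias of 0.05–0.09 on a true log odds ratio of 0.4, that is 0.05/0.4 = 12.5% to 0.09/0.4 = 22.5%. With site fixed, coverage was 0.95–0.97 and bias 0.01–0.03.

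**Step 4: the robust-error route, checked by hand.** At the fitted coefficients the two clusters' score totals sum to zero, so they are mirror images and the robust covariance has rank one. With the usual factor G/(G−1) = 2 and similar clusters, the Wald ratio behaves like a t variable on 1 df but is compared with 1.96. Coverage is then about (2/π)·arctan(1.96) = 0.70. The table gives 0.63–0.70, and a further run of 1,500 datasets (n = 170) gave 0.689, against 0.944 with site fixed. Across all runs the range is about 0.62–0.72.

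**The case against.** The strongest reply is that the reported results are odds ratios for factors that vary by patient or event, not the site variance. In its ordinary sense a hierarchical logistic model means a random intercept, and under that reading intervals for covariates balanced over sites are sound. This stands. The very wide interval for the between-site SD concerns a quantity that the article does not plan to report.

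A reader might infer that none of the model's confidence intervals can be trusted, or that coverage will be near 0.7. The article does not support either reading. The low coverage belongs to site-clustered robust errors, which it never names. Nor is it right that results must be either unadjusted for site or anti-conservative: a random intercept with a non-zero estimate adjusts in part.

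A second reply is that the article condenses a full analysis plan, available on request, which may settle how site enters. That excuses silence on implementation. It does not excuse what is stated: a hierarchical model, with site as the cluster, in a trial with two sites.

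A third reply is that the treatment comparison is untouched. This also stands: the primary and binary secondary outcomes use the site-stratified Mantel-Haenszel approach, and continuous outcomes a site-stratified rank test.

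**Conclusion.** The point holds as one of moderate weight. Two sites cannot support a useful between-site variance, so the hierarchical term offers no dependable site adjustment and no gain over a fixed site term. Under a random intercept the harm is limited to covariates that differ between the sites: coverage of about 0.90–0.945 and some residual site confounding. Which of the listed covariates differ is a plausible expectation from the two settings, not something the article reports. The serious loss of coverage arises only if robust site-clustered errors are used, a route the wording leaves open but does not state.

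The figures rest on an assumed 70/30 split, site SDs of 0 to 0.6 or a site log-odds gap of 0.4 to 0.7, and simplified covariates. The structural point, one degree of freedom, rests only on the number of sites. The secondary objective and the additional models for selected secondary outcomes are affected; the treatment comparisons are not.

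**What to change.** State that the secondary objective will be analysed by ordinary logistic regression with site (British Columbia or Columbus) as a fixed effect, with model-based or profile-likelihood intervals. Apply this to every secondary outcome given the same modelling approach, and state that site-clustered robust standard errors will not be used.

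The cost is one sentence and one model parameter. The results are then conditional on these two sites, and no effect of a purely site-level factor can be separated from site. Two sites could not support either inference in any case. The change brings the model into line with the site-stratified randomisation and primary test. Because the Blinding section keeps the group key sealed until the analysis is complete, it can be made without knowledge of allocation.

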## Knowledge dissemination

Results from this trial will be communicated through peer-reviewed publication, scientific conference presentations, posting on ClinicalTrials.gov. A plain language summary will be developed and shared via institutional websites and social media. We will also engage paramedic services, public health units, and CPR advocacy organizations to share findings with community members, lay responders, and healthcare professionals in participating regions.

## Trial management

The trial is coordinated from Queen’s University in Kingston, Ontario. Oversight is provided by a steering committee comprising of the principal investigator, lead research coordinator, co-investigators, technical representatives from participating sites, and research personnel responsible for local implementation and data collection. The committee meets bi-monthly to monitor study progress, review reports of adverse events, and address operational challenges. An independent Data and Safety Monitoring Board (DSMB) is guided by a charter to provide external oversight. DSMB members have expertise in clinical trials, resuscitation science, paramedic service operations, paramedicine, and emergency medicine. The DSMB meets every six months to review maintenance of equipoise, patient safety, enrollment rates, protocol adherence, and data quality. Within 48 h after each meeting, the DSMB provides a report to the principal investigator recommending continuation, modification, or termination of the study. A copy of the DSMB charter can be obtained from the corresponding author. Protocol modifications are reported to all site PIs, the DSMB, and all relevant research ethics boards.

## Trial progress to date

The trial launched on June 8, 2021 in Columbus and July 30, 2021 in British Columbia. As of May 12, 2025, a total of 288 patients have been successfully enrolled and included in the primary analysis dataset. We anticipate completing enrollment by December 1, 2025.

## Discussion

Crowdsourcing applications like PulsePoint Respond, which alert nearby lay responders to suspected cardiac arrests, offer a novel approach to improving early resuscitation. While observational studies and system-level evaluations suggest possible benefits^16^, ^17^, ^18^, ^19^, ^20^, ^21^, ^22^, ^23^, ^24^, ^25^, ^26^, ^27^, ^28^, ^29^, ^30^, evidence from randomized trials remains limited. Only one published RCT has evaluated crowdsourcing technology for OHCA, but it involved a text-message based intervention in a Scandinavian setting, included private residential locations, was only active during the daytime, and did not involve notification of nearby public AED locations.^10^ The benefit observed in this trial was encouraging, but modest. The intervention increased bystander CPR by 13.9 percentage points without any significant increase in survival.

Despite the paucity of data from clinical trials, this approach has proliferated. We conducted a scoping review of the literature which identified an 25 different crowdsourcing technologies being used in 15 countries around the globe.^31^ At the time of writing, PulsePoint has been implemented in over 5300 U.S. communities and has more than 1.3 million app users.^32^ This widespread adoption without more evidence from clinical trials is problematic. Observational studies such as pre-post comparisons or analyses of alerted vs. non-alerted cases, are prone to significant bias. Bystander CPR rates could increase over time due to unrelated public health initiatives, and alerts tend to occur in densely populated areas where circumstantial bystanders are more likely regardless of the app. These factors could result in an overestimate of the true impact of the technology.

In this context, clinical equipoise remains due to uncertain benefit, associated costs, and potential risks of crowdsourcing technology. Agencies adopting the technology incur expenses related to software licensing and the human resources required for program management, and ongoing public engagement. Theoretical risks include potential injuries to responders en route, liability issues for hosting agencies, unsafe scene conditions for responders, and risks to patient safety through poor-quality CPR, privacy breaches, and theft. These uncertainties underscore the need for high-quality evidence from clinical trials to determine whether the benefits of crowdsourcing technologies for OHCA justify their costs and potential risks.

This has been a very challenging trial to implement and manage. Of the five originally proposed study sites, only two were ultimately able to participate. Concerns related to legal liability for the hosting agency, specifically around the randomization of cardiac arrest patients and the sharing of patient data prevented participation of proposed sites in Toronto, Oshawa, and Winnipeg. Despite several years of engagement with these sites and successful technical implementation of the PulsePoint system we were unable to reach a resolution on these issues and efforts to implement the trial in these places were abandoned.

Technical hurdles contributed to significant delays. In British Columbia, accurately distinguishing public from private locations during 9-1-1 calls was essential for determining trial eligibility, as the PulsePoint Respond app was initially designed to notify for public-location arrests only. To support public-only alerts, the Foundation developed custom geolocation coding for BC, and delays in its development, implementation, and testing postponed the site’s launch by several months. The COVID-19 pandemic introduced disruption and delays to trial implementation. Concerns about infection risk among lay responders, paramedics, and firefighters led to a delayed launch of the study for nearly a year. After launch, both active study sites experienced intermittent downtime due to cybersecurity threats, CAD software upgrades, and technical malfunctions. Even after all these issues were resolved, recruitment has been slower than projected, primarily due to limited public uptake of the PulsePoint app and the restrictive inclusion criteria necessary for a scientifically rigorous evaluation. A key contributor to this challenge was the lack of dedicated funding for community outreach, marketing, or communications. The study budget did not include resources for promotional activities, and the hosting agencies, while very supportive, had limited capacity to fund or lead sustained public engagement campaigns. As a result, all efforts to promote PulsePoint uptake in participating communities were conducted in-kind, using low-cost strategies.

Our methodology has some limitations. We are using a modified intention-to-treat approach which includes only paramedic-treated cardiac arrests in the analytic cohort. Because paramedic resuscitation must be initiated to meet inclusion criteria, the presence of a bystander responder, especially one delivering CPR, could influence paramedic decision-making and increase the likelihood of paramedic treatment. This could lead to differential post-randomization exclusion between groups and introduce selection bias. Importantly, the direction and magnitude of this bias depend on the true effect of the PulsePoint intervention. If PulsePoint increases bystander CPR, more cases in the intervention group may meet inclusion criteria, potentially exaggerating the observed effect. If PulsePoint has no impact, exclusions may be more balanced, and bias minimized. Both participating paramedic services follow structured, protocol-driven criteria to guide treatment decisions, including defined indicators for withholding or terminating resuscitation, which helps to reduce subjective variation. Nonetheless, the potential for selection bias due to pre-eligibility randomization remains and will be considered when interpreting trial findings.

This trial addresses the urgent need for innovation in OHCA response. Bystander CPR and AED use remain far too low, and the status quo is not acceptable. We pursued this complex public intervention because new strategies must be evaluated with scientific rigor. Despite significant challenges, this study is uniquely designed, with automated real time randomization and blinding integrated into dispatch systems. Its findings will provide rare and valuable evidence to guide future policy, innovation, and refinement of this promising new approach to OHCA.

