### Sample size considerations

We calculated our target sample size to detect a 15 % absolute increase in bystander resuscitation attempts between treatment groups. The study steering committee determined this to be the minimal clinically important difference through consensus. Using updated simulations assuming a consistent odds ratio across strata with varying baseline event rates, we initially targeted a total sample size of 522 patients to achieve 90 % power, assuming a two-sided alpha of 0.05. However, partway through the trial, we revised the target sample size due to slower-than-anticipated recruitment, limited funding, and concerns about the feasibility of an extended study duration. To address these constraints, we reduced the target power to 80 %, yielding a revised sample size of 340 patients (170 per group). We did not account for missing patients in our revised calculations because recruitment data at the time indicated <1 % loss to follow-up.

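### The limitation on paramedic-treated selection gives one direction of bias, exaggeration, but the direction depends on effect scale, control rate and selection path, and for the reported relative risk the simplest path points the other way

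*Protocol article*

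**What the plan says.** The primary cohort is formed after randomization and keeps only arrests that paramedics treated (Protocol article, Primary analysis eligibility and case confirmation). The limitations paragraph of the Discussion accepts that a bystander responder on scene, above all one giving CPR, could make crews more likely to treat. It then gives the consequence: "If PulsePoint increases bystander CPR, more cases in the intervention group may meet inclusion criteria, potentially exaggerating the observed effect". It adds that bias should be small if the app has no impact, and that the issue will be weighed when the results are interpreted.

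The primary outcome is bystander CPR or AED use before professional responders arrive (Outcome measures). Under Analysis plan, "Estimates of the treatment effect will be reported as absolute risk differences and relative risks". Adjusted odds ratios appear there for the hierarchical logistic model that serves the secondary objective and for selected binary secondary outcomes. None is named for the primary comparison. Sample size considerations says the simulations were run "assuming a consistent odds ratio across strata with varying baseline event rates".

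**The concern.** The variable said to drive inclusion, bystander CPR, is a component of the primary outcome. Selection on an outcome acts in both arms: control patients who received CPR are over-included as well. More alert-arm cases entering the cohort therefore does not by itself widen the contrast, and on a ratio of risks it narrows it.

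The article promises to use this limitation when reading the results. With only exaggeration on record, a reader could mark down a positive relative risk as inflated when the simplest form of the stated mechanism makes it too small. A reader of the risk difference could be right or wrong, depending on a control rate that the article does not give.

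**Working it through.** **Inputs.** Sample size considerations gives the target effect: "We calculated our target sample size to detect a 15 % absolute increase in bystander resuscitation attempts between treatment groups". Power is 80%, "assuming a two-sided alpha of 0.05", and the revised total is 340. The control rate in the cohort is not given; the Introduction has only a general figure of under 50% for bystander CPR. The strength of selection is not given either. Both are assumed here and varied.

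**Reproducing 340.** Per arm, n = [1.960√(2p̄(1−p̄)) + 0.842√(pC(1−pC)+pT(1−pT))]² / 0.15². For 50% v 65%, p̄ = 0.575 and n = 169.3, so 170 per arm and 340 in all. By symmetry 35% v 50% gives the same. The article used stratified simulations, so these rates are inferred. The same formula at 90% power gives 454, not the earlier target of 522, so the match is only a guide.

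**Path 1: inclusion depends on the outcome, equally in both arms.** Let k = P(treated | CPR/AED) / P(treated | neither). An arm with true rate p shows p* = kp/[1+(k−1)p]. It follows that:

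- OR* = OR, because the odds in each arm are multiplied by k.
- RR* = RR × [1+(k−1)pC]/[1+(k−1)pT], which is below RR whenever k>1 and pT>pC.
- RD* = k × RD / {[1+(k−1)pC][1+(k−1)pT]}. For k>1 this exceeds RD only if k > [1+(k−1)pC][1+(k−1)pT], that is, if pC + pT + (k−1)pC·pT < 1. For k near 1 this is roughly pC+pT<1.

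Example, 50% v 65% with k = 2: pC* = 1.00/1.50 = 0.667 and pT* = 1.30/1.65 = 0.788. Hence RD* = 12.1 points, RR* = 1.18 and OR* = 1.857, against true values of 15.0, 1.30 and 1.857.

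| True rates | Measure | True | k=1.1 | k=1.5 | k=2 |
|---|---|---|---|---|---|
| 10% v 25% | RD (points) | 15.0 | 15.9 | 19.0 | 21.8 |
| | RR | 2.50 | 2.46 | 2.33 | 2.20 |
| 20% v 35% | RD | 15.0 | 15.6 | 17.4 | 18.5 |
| | RR | 1.75 | 1.72 | 1.64 | 1.56 |
| 35% v 50% | RD | 15.0 | 15.2 | 15.3 | 14.8 |
| | RR | 1.43 | 1.41 | 1.34 | 1.29 |
| 50% v 65% | RD | 15.0 | 14.8 | 13.6 | 12.1 |
| | RR | 1.30 | 1.28 | 1.23 | 1.18 |

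With no true effect, this path produces no bias on any scale.

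**Path 2: presence without CPR also prompts treatment.** The article names presence as well as CPR. Illustration at 50% v 65%: inclusion is 0.95 with CPR and 0.70 without; 40% of alert-arm cases without CPR have an alerted responder present and are included at 0.85. Mean inclusion without CPR in the alert arm is 0.6×0.70 + 0.4×0.85 = 0.76. Then pC* = 0.475/0.825 = 0.576 and pT* = 0.6175/0.8835 = 0.699, so RD = 12.3 points, RR = 1.214 and OR = 1.857×0.70/0.76 = 1.711. With no true effect on the outcome (50% in both arms), pT* = 0.475/0.855 = 0.556, RR = 0.965 and OR = 0.921.

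**Path 3: CPR sways crews more in the alert arm.** At 50% v 65%, inclusion with CPR is 0.95 (alert) v 0.85 (control), and 0.80 without CPR. Then RD = 17.3 points, RR = 1.336 and OR = 2.076. All rise.

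**Path 4: arrests that never get a responder are the least treatable.** Half the cases receive CPR in either arm (inclusion 0.90). Another 15% receive it only if alerted (0.90 without CPR, 0.95 with). The other 35% never do (0.60). Then pC* = 0.450/0.795 = 0.566 and pT* = 0.5925/0.8025 = 0.738, so RD = 17.2 points, RR = 1.304 and OR = 2.163.

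**The case against.** The limitation is hedged, names no effect scale, sits in the Discussion and fixes no analysis. On the risk difference, which the plan reports, exaggeration is possible: with a control rate of 10–20% and k of 1.5–2 it is material, and the article gives no cohort rate that rules this out. Paths 3 and 4 can also inflate. The full analysis plan is not shown and may contain sensitivity analyses. All of this stands. It is why the point is that the direction is incomplete, and wrong for the relative risk on the simplest path; it is not that exaggeration is impossible.

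A reader might go further in four ways that the documents do not support:

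- *That the odds ratio is immune.* It is preserved only on path 1; paths 2 to 4 all move it, and path 2 is part of the article's own description.
- *That the risk difference hardly moves.* This holds only near the inferred planning rates with weak selection.
- *That inflation requires CPR to influence crews more in the alert arm.* Path 4 raises the risk difference and the odds ratio without that, although the relative risk barely changes. The eligibility section ties withholding of treatment to signs of irreversible death, so unequal treatability is plausible.
- *That the plan reports no odds ratios.* It reports adjusted ones in the secondary model; only the primary comparison lacks one.

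In the other direction, low control rates fit the planned size poorly (the same formula gives totals of 200 at 10% and 276 at 20%), and the cohort is confined to public arrests with an app user within 400 m. That makes such rates less likely but does not exclude them, given simulations with rates varying by stratum.

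**Conclusion.** The concern holds in limited form. A single stated direction is not justified. If the outcome raises the chance of treatment equally in both arms, the relative risk is biased toward 1 for every k>1. The loss is 0.02 to 0.12 on a true 1.30, or 0.02 to 0.14 on a true 1.43, for k from 1.1 to 2. The risk difference can go either way, as tabulated. The statement that bias is small when the app has no impact holds on path 1. It fails on path 2 if the app brings responders to the scene without changing the outcome. The sizes rest on assumed control rates and inclusion probabilities; the sign for the relative risk on path 1 is algebra and does not. Nothing here shows that the trial's eventual result will be too large or too small.

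**What to change.** 1. In the Discussion, replace the single direction with a statement by scale and path. For outcome-dependent inclusion that is equal in both arms: relative risk toward 1, odds ratio unchanged, risk difference up or down according to the two rates. For responder presence without CPR: all three pulled down, even with no true effect. For arm-specific influence on crews, or lower treatability of arrests without a responder: possible inflation.
2. In the Analysis plan, add the site-stratified Mantel-Haenszel odds ratio with 95% confidence interval as a supplementary estimate for the primary comparison. Describe it as robust only to inclusion that depends on the outcome equally in both arms.
3. Add a short table correcting the risk difference and relative risk for k from 0.8 to 2, using p = p*/[k−(k−1)p*] in each arm within site. Values below 1 cover bystander-treated patients who drop out because they recover before the crew acts.
4. Report exclusions for non-treatment by arm, so that readers can see whether selection was differential.

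The cost is one more estimate from tables already required, one sensitivity table and a less simple limitation. No new data are needed.
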